### Statistical analyses

2.9

Reporting will follow CONSORT E-Health standards (Eysenbach and Consort-Ehealth Group, 2011). The primary outcome is the change in the composite score of SPS & SIAS from baseline to eight weeks (post-treatment). The analyses are carried out on the basis of the intention-to-treat approach (ITT; i.e., using all randomized participants). Our primary interest is in testing the main effects and interactions. For that, we will use linear mixed models repeated measures analysis of variance (ANOVA). This approach uses all available data on each subject and does not require the imputation of missing values but estimates parameters about missing values. Furthermore, mixed models account for the correlation between the repeated measurements. Main effects and interactions are calculated based on aggregates across experimental conditions. The levels of the factors will be represented numerically by −1 (absence of a component in a condition) and +1 (presence of a component in a condition), as recommended by Collins (2018). Significance testing of dichotomous data such as diagnostic status will be conducted with chi-square tests. Sensitivity analysis will be conducted to analyze the impact of dropouts on our results.

We will test mediation of the hypothesized change mechanisms (i.e., knowledge gain of SAD, decrease of dysfunctional social cognitions, decrease of self-focused attention, decrease of avoidance and safety behaviors) of the effect of the treatment components on primary and secondary outcomes (see Fig. 2 above). We will test mediation of the hypothesized change mechanisms by using an approach that allows multiple mediators in one model, as set out by Kraemer et al. (2002).

In addition, we will explore potential moderation of the treatment components by various measured variables (i.e., age, gender, country of origin, nationality, country of parents, mother tongue, relationship status, educational level, employment status, presence of comorbid disorder, use of medication, the severity of SAD). For the analysis of potential moderators, factorial ANOVA and multiple regression analysis will be used.

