##### Knowledge of SAD test (KSAD; Andersson et al., 2012; Berg et al., 2020a)

2.7.3.1

The KSAD assesses basic knowledge around the condition of SAD and its treatment. It includes 11 questions, each with one correct answer (out of three possible choices). In addition, each response is rated in terms of how confident the participant is about the response with three response options (Guessing, Pretty Certain, Confident). A higher score indicates more knowledge. Questions cover the content of the psychoeducation component of the Shyne program (e.g., the definition of SAD, general principles of CBT, safety behaviors, avoidance, negative automatic thoughts, attentional shift, exposure). Scores of knowledge of SAD are calculated in two ways: (a) a total score based on the total number of correct answers and (b) a weighted total score in which certainty of answers was factored in. Reliability analyses showed a low Cronbach's alpha of α  =  0.40 for the raw scores, a high Cronbach's alpha of α  =  0.86 for the certainty ratings, and an alpha of α  =  0.56 for the weighted scores (Andersson et al., 2012).

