##### Social cognitions questionnaire (SCQ; Wells et al., 1993; German version: Stangier et al., 1996b)

2.7.3.2

The SCQ is a self-rating scale that assesses typical negative social cognitions of socially anxious individuals. It is composed of 22 items, ranging from 22 to 110, grouped in three subscales (“negative self”, “performance anxiety”, and “fear of showing bodily symptoms”). Higher scores mean more negative social cognitions. The Cronbach's α for the whole German version scale is α = 0.89.

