##### Social Behaviors Questionnaire (SBQ; Clark et al., 1995; German version: Stangier et al., 1996a)

2.7.3.5

The SBQ assesses the use of safety behaviors in social situations with 27 items. The frequency of each behavior is rated on a 4-point scale (from 0 = never to 3 = always). “Avoid eye contact”, “try to control shaking”, “rehearse sentences in your mind” are examples of safety behavior assessed by the SBQ. The items on the SBQ are a mixture of discrete behaviors (e.g., hide your face, grip glasses tightly) and broad strategies (e.g., make an effort to come across well, try not to attract attention). Studies with adult populations revealed acceptable internal consistencies (Cronbach's α = 0.69).

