Finally, the measure of knowledge gain (KSAD; Andersson et al., 2012; Berg et al., 2020a) might represent a limitation since the original authors have not found satisfactory reliability. We will replicate the reliability and test-retest analysis with our sample using all time points available to re-evaluate the ability of this scale to capture change in knowledge gain.

We aim to perform mediation analyses to test the hypothesized mechanisms of change. The mere statistical mediation is not enough to ascertain a mechanism of change (Kazdin, 2007). The field needs to show a solid theoretical foundation for a specific mediator and also strong statistical association, temporality (i.e. timeline shows that intervention leads to change in mediator which leads to change in outcome, not the other way around), specificity (i.e., to prove that one particular mediator is responsible for change), gradient (i.e., dose-response relationship between mediator and outcome), consistency (across studies with different samples) and coherence with other evidence, for instance, results coming from experimental studies (Kazdin, 2007). In our study, we will be able to assess temporality, specificity and the gradient of theoretically founded mechanisms of change. Although other studies will be needed to evaluate consistency and coherence with other experimental evidence, our results might move forward theoretical debates regarding the mechanisms involved in the maintenance of SAD and what works in treatments. We estimate that this trial's results will inform the treatment of social anxiety via internet interventions and inform face-to-face treatments. At a societal level, optimizing treatment and expanding the knowledge about mechanisms of change is essential because SAD is very common and one of the costliest psychiatric conditions (e.g., Fehm et al., 2005). By determining the importance of each component to the overall efficacy of CBT treatment for SAD, we will be able to inform mental health policy decisions that would probably decrease its costs and increase its effectiveness.

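### The planned multiple-mediator model makes no stated allowance for measurement error, although the scales' alphas run from 0.40 or 0.56 (knowledge) to 0.92 (avoidance), so the comparison of mechanisms would partly reflect scale reliability

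*Protocol article*

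**What the plan says.** Section 2.9 names the mechanisms as gain in knowledge, and decreases in dysfunctional cognitions, self-focused attention, and avoidance and safety behaviours. It tests them "by using an approach that allows multiple mediators in one model", following a cited method. It does not say whether scores are observed or latent, or how change is represented, and it mentions no correction for measurement error.

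Sections 2.7.3.1 to 2.7.3.5 give the internal consistencies:

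- KSAD: "0.40 for the raw scores" and "0.56 for the weighted scores". Section 2.7.3.1 adds that "Scores of knowledge of SAD are calculated in two ways" and does not say which score is the mediator.
- SCQ (cognitions): 0.89.
- SCS (self-focused attention): 0.87 and 0.86 for its two subscales.
- LSAS-SR avoidance: 0.92.
- SBQ (safety behaviours): 0.69, introduced with "Studies with adult populations revealed acceptable internal consistencies".

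The Discussion (section 3) accepts that the KSAD may be a limitation because "the original authors have not found satisfactory reliability", and plans to repeat the reliability and test-retest analyses in the trial sample. It states no consequence for the mediation model. Its next paragraph says the study will be able to assess specificity, which it explains as showing that one particular mediator is responsible for change.

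**The concern.** Random error in a mediator shrinks its path to the outcome. When several mediators with different reliabilities share one model, the poorly measured ones look weaker and the well-measured ones look stronger, even if all matter equally. Which mechanisms mediate is a stated secondary objective (section 1.1), and a specificity claim compares paths within one model. A weak or null knowledge path could then be taken to mean that psychoeducation does not act through knowledge, when it partly reflects an 11-item test with low alpha. The same applies, less strongly, to safety behaviours, for which the protocol gives no caveat.

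**Working it through.** The protocol states no mediation effect size or power, so there is no figure to reproduce. The check asks what a model with uncorrected scores would estimate in a large sample.

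**Inputs from the protocol.** Reliabilities (alpha taken as reliability): KSAD 0.40 or 0.56, SCQ 0.89, SCS 0.87, LSAS-SR avoidance 0.92, SBQ 0.69.

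**Assumptions.** One score per scale gives five mediators. True paths are equal. The protocol gives no mediator correlations, so the true-score correlation ρ within condition is set at 0, 0.3 and 0.5. Because alpha may understate the reliability of a mixed-content test, KSAD 0.70 is also tried.

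**Formula.** With R the true correlation matrix, D = diag(1/rel − 1) and b the true paths, the estimated paths are (R + D)⁻¹ R b. For equal paths and a common ρ, the fraction retained by mediator i is

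(1 + 4ρ)/cᵢ ÷ (1 + ρ Σ 1/cⱼ), with cᵢ = 1/relᵢ − ρ.

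**Worked case, ρ = 0.5, raw KSAD.**

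- c = 2.000 (KSAD), 0.624 (SCQ), 0.649 (SCS), 0.587 (avoidance), 0.949 (SBQ).
- Σ 1/c = 0.500 + 1.604 + 1.540 + 1.704 + 1.053 = 6.401.
- Common factor: 3 / (1 + 0.5 × 6.401) = 3 / 4.200 = 0.714.
- KSAD keeps 0.714 × 0.500 = 36%. Avoidance shows 0.714 × 1.704 = 122%.

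**Estimated path as a percentage of the true path.**

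| Mediator | ρ = 0 | ρ = 0.3 | ρ = 0.5 |
|---|---|---|---|
| KSAD raw (0.40) | 40 | 40 | 36 |
| SBQ, with raw KSAD | 69 | 77 | 75 |
| SCS, with raw KSAD | 87 | 104 | 110 |
| SCQ, with raw KSAD | 89 | 107 | 115 |
| Avoidance, with raw KSAD | 92 | 112 | 122 |
| KSAD weighted (0.56) | 56 | 58 | 54 |
| Avoidance, with weighted KSAD | 92 | 109 | 118 |
| KSAD if reliability is 0.70 | 70 | 74 | 72 |

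Intermediate correlations change the KSAD figures by only about one percentage point.

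**Apparent ratio of avoidance to knowledge (true ratio 1)** = (1/rel_KSAD − ρ) / (1/0.92 − ρ):

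- raw KSAD: 2.3, 2.8, 3.4
- weighted KSAD: 1.6, 1.9, 2.2
- KSAD at 0.70: 1.3, 1.4, 1.6

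A simulation with 400,000 records at ρ = 0.3 and true paths of 0.20 gave knowledge paths of 0.080 (raw) and 0.117 (weighted), against 0.080 and 0.116 from the formula. If all five scales had reliability 0.89, each would take 20% of the summed paths at every ρ tried, so unequal reliability is what drives the distortion.

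**If only knowledge truly acts.** KSAD keeps 40, 36 and 30% (raw) or 56, 51 and 44% (weighted). For a true knowledge path of 1, with the raw score, each other mediator picks up 0 at ρ = 0, 0.07–0.10 at 0.3 and 0.09–0.15 at 0.5.

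**Where the lost part goes.** Assume psychoeducation moves knowledge by 0.5 and each other mediator by 0.1, all true paths are 0.3, ρ = 0.3, and the raw score is used. The true indirect effects are 0.5 × 0.3 = 0.150 through knowledge and 4 × 0.1 × 0.3 = 0.120 through the rest. The model gives 0.060 through knowledge, and the other four still total 0.120. The missing 0.150 − 0.060 = 0.090 appears as a direct effect.

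**Gain scores.** The reliability of a gain is about (rel − r)/(1 − r), with r the pre-post correlation. For raw KSAD this is (0.40 − 0.20)/0.80 = 0.25 at r = 0.2 and (0.40 − 0.30)/0.70 = 0.14 at r = 0.3. Raw gains would therefore usually make matters worse, by an amount that depends on an r the protocol does not give for this scale.

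**The case against.** The best defence is that section 2.9 does not specify observed scores. A condensed article may leave the treatment of measurement error to the analysis plan, and the words gain and decrease name mechanisms rather than define gain-score variables. That stands: observed scores are an inference from the absence of any latent or corrected model. By itself, that silence would not be a finding. What makes it one is that the article itself raises the poor KSAD reliability, limits its response to re-estimating it, and then says specificity can be assessed.

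Several stronger readings are tempting but not supported:

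- *The knowledge path is cut by more than half.* With equal paths this holds only for the raw score. For the weighted score the cut is 42–46%, and it passes half only if knowledge alone acts and mediators correlate at about 0.35 or more.
- *The lost share moves to the other mediators.* This needs correlated mediators. At ρ = 0 nothing moves to them, and in the example above the loss shows up as a direct effect.
- *With gain scores only 14–16% of the knowledge path survives.* This rests on an assumed r of 0.3 for KSAD and 0.5 for the other scales. With KSAD at r = 0.1 the figure is 33–38%. At r = 0.5 the formula gives (0.40 − 0.50)/0.50 = −0.20, which is impossible.
- *The authors will rank mediators or treat a null knowledge path as disproof.* The protocol does not say so. It warns that statistical mediation alone does not establish a mechanism, calls this work exploratory in section 1.1, and powers the trial for the component effects only (section 2.8).

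It is also fair that alpha is not retest reliability, and that 11 items of varied content may be more reliable than alpha suggests. That shrinks the distortion without removing it: at 0.70 the avoidance path still looks 1.3 to 1.6 times the knowledge path.

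**Conclusion.** The concern holds in a limited form. If observed scores enter the single model, the comparison of mechanisms partly reflects how well each scale measures. With equal true paths, avoidance would look 2.3–3.4 times as strong as knowledge with the raw KSAD and 1.6–2.2 times with the weighted one. The direction was the same at every correlation tried.

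The size rests on assumptions: alpha as reliability, equal true paths, one score per scale and mediator correlations of 0 to 0.5. The protocol names four mechanisms, with avoidance and safety behaviours listed together, so five mediators is also an assumption.

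A reader might infer that the reliability-corrected model should replace the planned one. The material does not support that. Correcting with 0.40 when the true reliability is 0.70 would inflate the knowledge path 0.70/0.40 = 1.75-fold even with uncorrelated mediators. The primary component analysis is unaffected. This matters for a stated secondary objective, and the plan should address it before the mediation results are read.

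**What to change.** In section 2.9 (or the analysis plan behind it):

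1. Keep the planned multiple-mediator model and add a sensitivity analysis corrected for measurement error. One option is a single-indicator latent variable per mediator, with error variance fixed at (1 − reliability) × observed variance.
2. Use the in-sample KSAD reliability that the Discussion already plans, and estimate the other scales' reliabilities in the same way. Repeat the analysis with KSAD reliability over a stated range, for example 0.40 to 0.70, which spans both published alphas and a more favourable value.
3. Enter each mediator with its baseline as a covariate, not as a raw gain.
4. State that a null KSAD path in the uncorrected model will not be read as evidence against the knowledge mechanism, and that specificity will not be claimed, nor mediators ranked, on uncorrected paths alone.

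This needs no new data or participants, only analysis-plan wording and modest extra modelling. The price is wider intervals for the KSAD and SBQ paths, and dependence on the assumed reliability, which the stated range makes visible.

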### Objectives

1.1

The primary objective of this trial is to investigate the active ingredients of ICBT for SAD by testing the main effects and interactions for the four main treatment components (i.e., psychoeducation, cognitive restructuring, attention training, and exposure) on primary (i.e., decrease in social anxiety symptoms) and on secondary outcomes (i.e., decrease in depressive symptoms, decrease in general anxiety, increase of quality of life, and client satisfaction). Furthermore, we also aim to investigate the effects of each treatment component on hypothesized change mechanisms and explore whether and which change mechanisms mediate the effect of the treatment components on symptom reduction. The specific secondary objectives (1) to investigate whether the specific mechanisms (i.e., knowledge gain of SAD, decrease of dysfunctional social cognitions, decrease of self-focused attention, decrease of avoidance and safety behaviors) mediate the effect of the treatment components on primary and secondary outcomes, and (2) to address additional exploratory research questions, including examining the negative effects of the treatment components and potential moderators of treatment outcome.

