### Sample size

2.8

The current study is powered for the first and primary research question, i.e., the main and interaction effects of the treatment components on the decrease of social anxiety symptoms. In the a priori power analysis, we assumed that the smallest clinically relevant difference would be a small effect size of Cohen's *d* = 0.2 for the main effect of an individual treatment component or interaction between components on pre-to-post change on social anxiety symptoms. Smaller effect sizes would be of little clinical interest and value. At an α level of 0.05, a statistical power (1-Beta) of 0.80, and a correlation between measurements with around 4- and 8-weeks interval of *r* = 0.50, based on our experience with clinical trials for SAD, we need a total of 384 participants (G*Power; Faul et al., 2007). Based on the finding that in 15 out of 17 studies, dropout rates (i.e., not providing assessment data at post-treatment) for ICBT for SAD were below 13% (Boettcher et al., 2013), we conservatively estimate a dropout rate of 20% for our study (*n* = 77 participants). Thus, we aim for a sample size of 464 participants, which results in 29 individuals per treatment condition.

As mentioned above, the logic behind how an experiment is powered differs between RCTs and factorial experiments. An RCT would compare the 16 conditions to each other, and power would be reflected in the per-condition sample size. If an RCT has a small per-condition sample size, such as 29 individuals per treatment condition, it does not have enough power to detect small effect sizes. By contrast, in factorial experiments, all participants receiving a specific component (e.g., cognitive restructuring, which is present in half of the conditions, i.e., in eight conditions) can be compared to participants who do not receive that component (also eight conditions, with 29 participants per condition). That yields a sample size of *n* = 232 per component (Collins, 2018). Since our study contains only components with two levels (absent vs present), the sample size to maintain the power to detect main effects and interactions is the same (Collins, 2018). For a detailed explanation of how factorial experiments maintain power to estimate main effects and interactions, see Collins (2018).

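### The moderator analyses name factorial ANOVA and multiple regression; in their usual form these would not keep all randomised participants, unlike the mixed model behind the component effects they qualify

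*Protocol article*

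**What the plan says.** All of this is in the protocol article.

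- **Population (2.9 Statistical analyses).** "The analyses are carried out on the basis of the intention-to-treat approach (ITT; i.e., using all randomized participants". The sentence is general and is not limited to the primary test.
- **Model for component effects (2.9).** For main effects and interactions: "For that, we will use linear mixed models repeated measures analysis of variance (ANOVA". The reason given is: "This approach uses all available data on each subject and does not require the imputation of missing values".
- **Model for moderators (2.9).** Twelve candidate moderators are listed, from age and gender to medication use and SAD severity. Then: "For the analysis of potential moderators, factorial ANOVA and multiple regression analysis will be used". The outcome, the time point and the handling of missing values are not given for this step.
- **Status.** Section 1.1 Objectives places moderators among exploratory questions ("to address additional exploratory research questions, including examining the negative effects of the treatment components and potential moderators of treatment outcome"), and 2.9 repeats this ("In addition, we will explore potential moderation of the treatment components by various measured variables").
- **Dropout.** Section 2.8 Sample size defines dropout as having no post-treatment assessment and plans for 20% ("we conservatively estimate a dropout rate of 20% for our study"). Section 2.9 adds: "Sensitivity analysis will be conducted to analyze the impact of dropouts on our results".

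**The concern.** A moderator effect is a component effect compared between subgroups, so it should rest on the same participants and the same missing-data assumption as the component effect. Factorial ANOVA and multiple regression need one outcome value per person. If that value is the week-8 score or the change to week 8, a participant without it has no row, and the week-4 score that the trial collected is not used.

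Two things follow if the methods are run in that usual form. First, the set analysed is not all randomised participants. Second, the missing-data assumption is stricter. The mixed model allows dropout to depend on scores already observed, including week 4. A completers' regression allows dependence only on what is in that regression. If people drop out according to how they were doing at week 4, and do so differently by component and subgroup, completers can show moderation that is not there. The subgroup effects also need not average to the reported component effect.

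**Working it through.** **1. The plan's own dropout figures.** Section 2.8 gives 384 evaluable participants and 20% dropout. 384 x 0.20 = 76.8, the 77 stated there. 384 + 77 = 461, which rounds up to 464 = 16 x 29.

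**2. Participants who would be left out.** At 20%: 464 x 0.20 = 92.8, about 93, leaving about 371. At 13%, the level that section 2.8 says most earlier studies stayed below: 464 x 0.13 = 60.3, about 60, leaving about 404.

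**3. Precision.** Assume r = 0.50 (section 2.8) between all waves, and unit variance. The residual variance of the week-8 score given baseline is v1 = 1 - 0.25 = 0.75. Given baseline and week 4 it is v2 = 0.667. Let n1 = 371 have week-8 data and n2 have week-4 data.
- Completers: v1/n1. Likelihood: v2/n1 + (v1 - v2)/n2.
- If every dropout gave week-4 data (n2 = 464), the ratio likelihood/completers is (0.667 + 0.083 x 371/464)/0.75 = 0.978, a gain of 2.2% in variance. If none did, the gain is 0%.
- Simulations under other assumed correlations put the completers' standard error 1% to 7% higher.

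**4. False moderation.** Assumptions: true moderation is zero, overall dropout is 20%, and in one component-by-subgroup cell dropout depends on the week-4 score (logit slope 0.7 to 1.2 per SD). The documents give no such pattern. Simulated false moderation, in SD:

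| Correlations assumed | Change score, completers | Baseline-adjusted, completers | Likelihood, all data |
|---|---|---|---|
| pre-mid 0.60-0.65, mid-post 0.75-0.80, pre-post 0.50 | 0.02 to 0.04 | 0.06 to 0.11 | about 0 |
| all 0.50 (the plan's value) | about 0 | 0.03 to 0.06 | about 0 |

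**5. Cross-check by formula.** Let d be the shift in the completers' mean week-4 score in the affected cell. The bias is roughly d times the covariance between the week-4 score and the analysed outcome.
- For a change score the covariance is r(mid,post) - r(pre,mid). That is 0.75 - 0.60 = 0.15, or 0.80 - 0.65 = 0.15, and 0 when all correlations are equal.
- For a baseline-adjusted outcome it is r(mid,post) - r(pre,post) x r(pre,mid). That is 0.75 - 0.30 = 0.45, or 0.80 - 0.325 = 0.475, and 0.50 - 0.25 = 0.25 when all equal 0.50.
- The first row's baseline-adjusted results imply d = 0.06/0.45 = 0.13 to 0.11/0.475 = 0.23. The change-score bias should then be 0.15 x 0.13 = 0.02 to 0.15 x 0.23 = 0.03. With all correlations at 0.50 the baseline-adjusted bias should be 0.25 x 0.13 = 0.03 to 0.25 x 0.23 = 0.06. Both agree with the table.

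**6. Scale.** Against the smallest relevant effect of 0.2, the worst cases are 0.04/0.2 = 20% and 0.11/0.2 = 55%. For a 50:50 moderator and 371 completers, the standard error of a difference between subgroup effects is 4/sqrt(371) = 0.21 for a change score (SD 1 at r = 0.50), and 4 x sqrt(0.75)/sqrt(371) = 0.18 when baseline-adjusted. The worst-case biases are therefore 0.04/0.21 = 0.19 and 0.11/0.18 = 0.61 standard errors. With k the bias in standard errors, a two-sided 5% test rejects with probability Phi(-1.96 + k) + Phi(-1.96 - k): about 5.4% and 9.4%.

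**The case against.** A reader might infer that the plan prescribes a completers-only moderator analysis and so contradicts its own all-randomised rule. The text does not support that. Section 2.9 never says complete-case, does not fix the outcome or time point for moderators, and does not rule out imputation or full-information estimation. The all-randomised sentence can be read as covering the moderator analyses too, and an analysis plan not shown may supply the detail. Exclusion is the default consequence of the named methods, not a stated rule.

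It can also be said that the analysis is exploratory, that a dropout sensitivity analysis is planned, that 20% is called conservative, and that the bias needs an assumed dropout pattern. With a change score and the plan's own r = 0.50 at all waves, the bias is about zero.

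Most of this stands and limits the weight of the point. What remains is that the article names a method class for moderators that differs from the one it chose for its handling of missing data. A later plan would have to change or supplement that named method, not merely fill a gap. The sensitivity analysis is described only in general terms and does not alter the main moderator estimate.

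**Conclusion.** The point holds in a limited form. Run in their usual way, the named moderator methods do not satisfy the all-randomised statement: about 93 of 464 would be left out at 20% dropout, about 60 at 13%. They also rest on a stricter missing-data assumption than the component effects. The precision cost is small and is not the reason to act.

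The possible bias is about 0 to 0.04 SD with a change score and about 0.03 to 0.11 SD with baseline-adjusted completers, against about zero by likelihood. These figures rest on dropout driven by the week-4 score in one component-by-subgroup cell, and on the assumed correlations. They show what could happen and do not predict what will. It would be too strong to say that the moderator analysis will show spurious effects: even the worst case is about 0.6 of a standard error. The primary inference is not affected. The change is still worth making, because it is cheap and aligns population, model and missing-data assumption.

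**What to change.** Replace the moderator sentence in section 2.9 with wording such as: *Each moderator is examined, as an exploratory analysis, by adding moderator x component x time terms, with all lower-order terms, to the mixed model used for the primary analysis. The week-8 contrast is the moderated effect, and all randomised participants are included.*

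Baseline SAD severity measured by the SPS and SIAS needs a variant, because it would otherwise be both a predictor and the baseline outcome in the same model. For that moderator, fit a mixed model to the week-4 and week-8 scores with baseline severity as covariate and severity x component x time terms. The small downside is that participants with no post-baseline score do not contribute to that one model, and this should be stated.

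If ANOVA or regression is kept, the plan should instead say how participants without a week-8 score stay in the analysis.

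The cost is one or two sentences. The mixed model is already being fitted, and no new data are needed.
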